#### Session 13 (week 20): assessment tools/questionnaires and recording of cancer-specific medications and treatments of patients

At the last session (at week 20), the patient will receive via email a link (generated by REDCap) to open in a web browser the questionnaires to be filled in (Patient’s Last Session questionnaire, FACIT-F, PSQI, PHQ-9, GAD-7, BPI, NCCN Distress Thermometer, arm mobility, and PRFS). The study nurse will retrospectively verify after the patient’s last session (at week 20) whether there were any changes in the therapy during the intervention period (Medical History and Treatments questionnaire). The same procedure will be followed in case of withdrawal.

#### Six- and 12-month follow-up assessments (from week 20)

Finally, the patient will receive via email a link (generated by REDCap) to open in a web browser the questionnaires to be filled in at 6-month and 12-month follow-up (Patient’s Follow-up questionnaire, FACIT-F, PHQ-9, GAD-7, BPI, NCCN Distress Thermometer, arm mobility, and PRFS). After the 12-month follow-up assessment, the study nurse will fill in the questionnaire “End of Study”. The same procedure will be followed in case of withdrawal.

#### Reminders

If a patient has not filled in the questionnaires after 2 days, she will automatically receive a reminder via email each day for a period of 5 days. The therapist will also remind the patient to fill in the questionnaires if necessary (status “Incomplete/Partial/Completed Survey Response” visible in REDCap).

### Withdrawal and discontinuation

Patients can withdraw anytime from the study should they wish to do so. They will be invited to specify the reason for withdrawal and to fill in the questionnaire “end of study”. All data gathered until withdrawal will be included in the analysis, as laid out in the informed consent document.

The oncologist, as well as the eurythmy therapist or physical therapist, can decide at any time to exclude the patient from the study, e.g. in case of concern due to disease progression. If possible, patients will be asked to fill in the end of study questionnaire at the time of withdrawal.

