## Methods/design

### Study design

The ERYT/CoordiFit study is a randomized controlled, open-label, two-arm, multi-center superiority trial. A sample of 196 female patients with metastatic breast cancer presenting with CRF will be randomly allocated to the intervention or control group in a 1:1 ratio. The control group is an active control intervention (CoordiFit) in order to control for unintended effects such as the therapist-patient interaction and active engagement (being part of a program). It consists of slow, standardized exercises that address physical coordination, stability, balance, and dexterity. These exercises are non-specific with respect to CRF and do not include mindfulness features. The study is planned to be conducted in 14 centers across Switzerland.

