### Study interventions

Both ERYT and CoordiFit exercises are easy to learn, and the training sessions will follow the same frequency and duration schedule, i.e., 13 standardized therapy sessions of 45 min (once a week for 6 weeks and then once every second week) during the total intervention period of 20 weeks. Patients are instructed by a eurythmy therapist or physical therapist, according to the group of allocation, in sessions with 1 to 4 patients. Therapists are available in all areas of Switzerland, either affiliated with institutions (e.g., hospitals) or work in private practices. Patients are asked to additionally train at home 15 min per day, 6 times a week, and compliance of the home training is reported by the patient in a diary.

All eurythmy and physical therapists will participate in an introductory teaching session before the start of the study, to familiarize themselves with the study specifics.

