#### Statistical analysis

A nonparametric ANOVA model for longitudinal data, the F1-LD-F1 model of Brunner, Domhof, and Langer, will be applied to model the course of the FACIT-F subscale scores from baseline over the whole intervention [77]. The first F1 means that there is one group factor, the second that there is one-time or repeated measures factor. The main hypotheses are the following:

H0: there is no interaction of the treatment arm with the time;

H1: there is an interaction of the treatment arm with the time (favoring ERYT).

Least-square means of the original data (original scales) and 95% confidence intervals will be calculated and displayed in figures over time.

Differences from baseline to end of intervention will be analyzed by stratified Wilcoxon rank-sum tests (via ordinal logistic regression, i.e., proportional odds model with baseline measurements as co-variable, treatment arm as binary predictor and differences as outcome variable). Least-squares means of the original differences and 95% confidence intervals will be calculated.

Exploratory endpoints will be analyzed descriptively using mean and standard deviation or median and interquartile, as appropriate.

Statistical analysis will be conducted applying an intention-to-treat approach, and therefore including all randomized patients. In case of protocol non-adherence, a per-protocol analysis will be conducted to estimate the robustness of the primary estimates. All tests will be two-sided with a significance level of 0.05. Statistical analysis will be performed using R [78].

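### The withdrawal rule lets staff who know the allocation end study participation, not just the sessions, and does not secure the remaining FACIT-F scores that the intention-to-treat comparison needs

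*Protocol article*

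**What the plan says.** Withdrawal and discontinuation (Protocol article) covers two routes out of the study. A patient may withdraw, and for this route the text says "All data gathered until withdrawal will be included in the analysis". In addition, the oncologist, the eurythmy therapist or the physical therapist "can decide at any time to exclude the patient from the study, e.g. in case of concern due to disease progression". Disease progression is an example; no closed list of grounds is given. On data at that point the section says: "If possible, patients will be asked to fill in the end of study questionnaire at the time of withdrawal". FACIT-F is not named there.

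Two other sections bear on this. The week-20 procedures list FACIT-F among the e-mailed questionnaires, then describe the study nurse's retrospective check of treatments, and end: "The same procedure will be followed in case of withdrawal". The section on the 6- and 12-month assessments ends with the same sentence, directly after the nurse's End of Study form.

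Study design calls this a "randomized controlled, open-label, two-arm, multi-center superiority trial". Study interventions states: "Patients are instructed by a eurythmy therapist or physical therapist, according to the group of allocation". The Statistical analysis section commits to "applying an intention-to-treat approach, and therefore including all randomized patients". The primary endpoint uses FACIT-F at baseline and weeks 8, 14 and 20.

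**The concern.** Stopping the sessions and leaving the study are different events, and the withdrawal section treats them as one. FACIT-F after baseline is completed through an e-mailed link, and the Discussion says that no hospital visits are scheduled during the intervention and follow-up. Nothing practical therefore requires the scores to end when the sessions end.

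The people who may end participation know the allocation, and the two therapist professions each decide on one arm only. The one ground named, disease progression, is plausibly related to fatigue. If the professions apply the open-ended rule differently, patients observed at weeks 8, 14 and 20 are selected differently by arm, and this enters the group-by-time comparison. An analysis plan can choose how to handle missing scores, but it cannot recover scores that were never requested.

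**Working it through.** **1. The plan's own dropout allowance.** Sample size gives 156 patients without drop-outs and 20% dropout: 156 / 0.80 = 195, or 196 for two equal arms. The stated 196 is reproduced. The issue here is bias, not sample size.

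**2. What is collected after exclusion, passage by passage.**
- Withdrawal section: data up to withdrawal, plus an end-of-study form where possible.
- Week-20 section, broad reading: the whole week-20 procedure, including one FACIT-F, is carried out at withdrawal. Narrow reading: only the nurse's treatment check is repeated.
- 6- and 12-month section: the same two readings.
- On neither reading does a patient excluded at, say, week 6 clearly receive FACIT-F at weeks 8, 14 and 20. The broad reading gives one off-schedule score.

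**3. Illustration of the bias.** Inputs from Sample size: SD 12 (the upper limit) and within-patient variation of 8 points (the upper limit). The text does not say whether 8 is the SD of a difference between two measurements, which gives 8/√2 = 5.66 per measurement, or the SD of each measurement, so both are used. The 20% dropout is applied to each arm.

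Assumptions that are not in the document: no true effect; normal scores with mean 30 and equal correlation between visits; dropout before week 20 in one arm depends on the week-14 score by a logistic model with odds ratio 2 or 3 per 10 points lower; dropout in the other arm is random. The eligibility cut-off is not modelled.

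Formulas:
- Correlation between visits: ρ = 1 − w²/144, with w the SD per measurement. For w = 5.66, 1 − 32/144 = 0.778. For w = 8, 1 − 64/144 = 0.556.
- Raw shift = mean week-20 score of retained patients in the selective arm − 30.
- Paired shift = raw shift − shift of the same patients' baseline mean. With equal correlations, selection on week 14 moves baseline and week 20 by the same amount, so this is about 0.
- Baseline-adjusted shift ≈ raw shift × (1 − b), with b the fitted slope on baseline (linear ANCOVA, standing in for the planned baseline-adjusted ordinal model).

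| w | Odds ratio | Raw week-20 shift | b | Baseline-adjusted shift | Paired shift |
|---|---|---|---|---|---|
| 5.66 | 2 | 1.39 | 0.772 | 1.39 × 0.228 = 0.32 | 0.0 |
| 5.66 | 3 | 1.95 | 0.767 | 1.95 × 0.233 = 0.45 | 0.0 |
| 8 | 2 | 0.99 | 0.550 | 0.99 × 0.450 = 0.45 | 0.0 |
| 8 | 3 | 1.39 | 0.545 | 1.39 × 0.455 = 0.63 | 0.0 |

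Against the planned 4 points, the raw shift is 0.99/4 = 25% to 1.95/4 = 49%, and the baseline-adjusted shift is 0.32/4 = 8% to 0.63/4 = 16%. With the same selection in both arms, the difference in shifts is 0 to within ±0.02.

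**4. A second assumed mechanism.** The zero for the paired change depends on step 3's assumptions. If exclusion instead follows the patient's own baseline-to-week-20 change (assumed correlation 0.5; 98 randomized per arm; completers only; 2,000 simulated trials per scenario), the mean bias in that change is:
- 20% v 20% excluded: −0.05 to −0.02;
- 25% v 15%: 0.6 to 0.8 points, with type I error about 0.05 to 0.08;
- 30% v 10%: 1.2 to 1.7 points, with type I error about 0.16 for the change and 0.11 for the interaction.

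The interaction test here is a parametric stand-in for the planned F1-LD-F1 model. No unequal dropout rates appear in the document.

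**The case against.** A reader might infer that the intention-to-treat analysis cannot be delivered. The document does not support that. FACIT-F is an entry criterion, so every randomized patient has a baseline value, and data up to withdrawal are kept. All patients can stay in the analysis set; what changes is that later values depend on assumptions.

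A reader might also infer that outcome collection certainly stops at exclusion. That is not stated either. The sentence "The same procedure will be followed in case of withdrawal" can be read as giving a final FACIT-F. This objection stands in part: the passages are ambiguous, but even the favourable reading supplies one assessment and not the remaining scheduled ones.

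Third, the 1.0 to 1.95 points could be taken as the expected bias in the primary result. They are not. They describe a raw week-20 difference among patients still observed, whereas the endpoint is change from baseline, tested as an interaction. An all-available rank analysis, which sets everyone's baseline against the remaining patients' later scores, could carry some of that shift. Under the same assumptions the paired change carries none.

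Fourth, the rule gives the oncologist and both professions the same power, and nothing shows that they would use it differently. This stands: differential exclusion is a risk created by the design, not a documented fact. For oncologists, knowledge of the allocation follows only from the open-label design.

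Finally, number, timing and reasons for attrition are already to be reported by group. That would reveal an imbalance but would not replace the missing scores. Missing-data methods may sit in an analysis plan that is not shown, so their absence is not counted here.

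**Conclusion.** The concern holds as a weakness in the withdrawal rule that should be corrected. Allocation-aware staff, with a different therapist profession in each arm, may end study participation on open-ended grounds, and continued FACIT-F collection is not secured. The later comparison of all randomized patients is then exposed to bias if exclusion depends on fatigue differently by arm.

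The size cannot be fixed from the document. It ranges from no mean bias (equal selection in both arms) to about 0.3 to 0.6 points after baseline adjustment and 1.0 to 1.95 points for the raw week-20 difference under the one-arm selection assumed in step 3. The paired change is unaffected there but not under every mechanism, as step 4 shows. Selection strengths and unequal dropout rates are assumptions throughout.

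**What to change.** Leave the clinical decision to stop sessions, and who takes it, unchanged. In Withdrawal and discontinuation:
- state that this decision ends the sessions only;
- state that FACIT-F continues to be e-mailed at weeks 8, 14 and 20 unless the patient withdraws consent;
- record who made the decision, alongside the reasons for attrition already reported by group.

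Reconcile the closing sentences of the week-20 and the 6- and 12-month sections with the withdrawal section, so that it is explicit which questionnaires are requested at withdrawal and which remain scheduled.

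The sample size stays at 196, and the planned F1-LD-F1 analysis need not be replaced. The cost is an amendment to the protocol and consent wording; the automatic e-mails and reminders already exist. The small downside is that some questionnaires will go to patients who no longer attend sessions.

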### Reporting of adverse events

Evidence suggests that SAEs are not anticipated [40, 49, 75, 76]. Potential minor AEs that may be anticipated are dizziness, headache, and tension pain in the back and/or arms [75].

All SAEs will be documented and reported immediately (within a maximum of 24 h) to the sponsor. Both the investigator and the sponsor make a causality assessment of the event to the trial intervention. Any event assessed as possibly, probably, or definitely related is classified as related to the trial intervention. Both investigator and sponsor make a severity assessment of the event as mild, moderate, or severe. Mild means the complication is tolerable, moderate means it interferes with daily activities, and severe means it renders daily activities impossible. If it cannot be excluded that the SAE occurring is attributable to the intervention under investigation, the investigator will report it to the Ethics Committee within 15 days. The SAEs that are a clear result of the underlying disease (e.g., events occurring due to breast cancer or metastasis) are events that will not be reported. AEs and SAEs that are ongoing at study end are followed up until resolution or stabilization.

An annual safety report is submitted once a year to the Ethics Committee by the sponsor.

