## Abbreviations

ANOVA: Analysis of variance
BPI: Brief Pain Inventory
CTU: Clinical Trial Unit
ECOG: Eastern Cooperative Oncology Group
ERYT: Eurythmy therapy
FACIT-F: Functional Assessment of Chronic Illness Therapy – Fatigue
FACT-G: Functional Assessment of Cancer Therapy – General
GAD: General anxiety disorder
HRV: Heart rate variability
MCID: Minimally clinically important difference
NCCN: National Comprehensive Cancer Network
PG-SGA: Patient-Generated Subjective Global Assessment
PHQ: Patient Health Questionnaire
PRFS: Patient-Reported Functional Status
PSQI: Pittsburgh Sleep Quality Index
SAE: Severe adverse effect

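### The adverse-event section sends every SAE to the sponsor within 24 h, then exempts disease-related SAEs from reporting without saying to whom the exemption applies

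*Protocol article*

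**What the plan says.** The section Reporting of adverse events in the protocol article sets out the rules in this order.

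- Sponsor route: "All SAEs will be documented and reported immediately (within a maximum of 24 h) to the sponsor". No exception is given.
- Causality: "Both the investigator and the sponsor make a causality assessment of the event to the trial intervention". Both parties also grade severity on a three-level scale that starts at mild.
- Ethics Committee route: where attribution of an SAE to the intervention cannot be ruled out, "the investigator will report it to the Ethics Committee within 15 days".
- Exemption, in the very next sentence, for SAEs plainly caused by the disease: "events occurring due to breast cancer or metastasis) are events that will not be reported". No recipient is named.

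The section opens with the expectation that "Evidence suggests that SAEs are not anticipated". It gives no SAE rate and no share of SAEs expected from the cancer. On blinding, the section Study design says: "The ERYT/CoordiFit study is a randomized controlled, open-label, two-arm, multi-center superiority trial". The list of abbreviations has "SAE: Severe adverse effect".

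**The concern.** A site with an SAE that it believes comes from the cancer finds two instructions. One says that all SAEs go to the sponsor within 24 h. The other says that this kind of SAE is not reported. The text does not settle which one governs.

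If the site follows the second, the sponsor receives no report and cannot make the causality assessment that the same section requires of it. The attribution then rests on one party, the site, whose staff know the arm. A second assessment protects against attribution that differs between arms, and it would be missing for the events where the first attribution decides whether anyone else looks. Regular on-site visits are not planned (section On-site monitoring visit(s)), so a later check on that attribution is less certain.

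**Working it through.** The plan states no figure that could be reproduced here. The check is a comparison of the sentences under the two possible readings, followed by an illustration of size.

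**1. Literal reading: the exemption covers all reporting.** The sponsor rule covers all SAEs, and the exemption removes some of them. Both cannot hold. For the exempted events the sponsor's causality assessment cannot take place as described, because the sponsor is not told of the event. Documentation is not removed: the first rule asks for documenting and reporting, and the exemption speaks only of reporting.

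**2. Narrow reading: the exemption covers only the Ethics Committee.** The sponsor rule then stays intact and there is no conflict. But the preceding sentence already limits the Ethics Committee route to SAEs for which attribution to the intervention cannot be excluded. An SAE plainly caused by the cancer is outside that route before the exemption is read. On this reading the exemption clarifies and changes nothing in practice. It alters what a site does only if it reaches the sponsor route.

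**3. What the wording settles.** The other two SAE reporting sentences each name their recipient (sponsor; Ethics Committee). The exemption names none. The narrow reading is plausible from its position, but it has to be supplied by the reader.

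**4. Size, under assumptions only.** From the protocol: 196 patients, 98 per group. Let r be the assumed proportion of patients with an SAE and s the assumed share of these whose SAE is judged plainly disease-related, counting one SAE per patient. On the literal reading:

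- Patients with an unreported SAE = 196 × r × s. Low end: 196 × 0.10 × 0.25 = 4.9, about 5. High end: 196 × 0.40 × 0.90 = 70.6, about 71.
- Patients per arm with a reported SAE = 98 × r × (1 − s). With r = 0.20 there are 98 × 0.20 = 19.6 patients with an SAE per arm. Those still reported are:

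| s | 98 × 0.20 × (1 − s) |
|---|---|
| 0.25 | 14.7 |
| 0.50 | 9.8 |
| 0.75 | 4.9 |
| 0.90 | 2.0 |

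The result follows the assumed share s, about which the documents say nothing. The range shows only that the size cannot be fixed from this protocol.

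**The case against.** The strongest reply is that the exemption directly follows the Ethics Committee sentence and reads as its complement: possibly related events go to the committee, plainly disease-related ones do not. That reading keeps the section consistent, and a charitable reader would choose it. A condensed article may also have lost a recipient that the full protocol names. This stands to the extent that the intent may well have been the narrow one. It does not remove the problem, because the printed sentence does not say so and, on that reading, was not needed.

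Other parts of the reply stand in full, and they limit the point:

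- A reader might infer that most SAEs would go missing. That needs a disease-related share above 50%, and the documents give no share.
- A reader might infer that the events are lost altogether. The requirement to document all SAEs remains and may keep them in site records.
- A reader might infer that a planned safety comparison between arms is compromised. The article lists no safety endpoint and describes no between-arm SAE analysis. Its description of the trial as low-risk is a premise of the design, not a conclusion from its SAE data.
- A fall or fracture during training is a poor example. Attribution to the intervention could hardly be excluded, so such an event belongs on the Ethics Committee route.
- The section does not say who decides, or when, that an event is plainly due to the disease. That the site decides alone follows only from the literal reading, under which the sponsor is not informed.

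**Conclusion.** The point holds as a conflict between stated rules. The section requires sponsor reporting and a double causality assessment for all SAEs, then exempts disease-related SAEs from reporting with no recipient named. On the literal reading, arm-aware site staff could withhold SAEs that they attribute to the cancer from the sponsor's required assessment. On the narrow reading nothing is withheld, and the text does not decide between the two.

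This is a risk created by the wording, not a demonstrated loss of safety data. The number of SAEs concerned is unknown; the range of about 5 to 71 patients rests wholly on assumed rates and on the literal reading. The sentences should still be corrected, because the sponsor's oversight of SAEs depends on which one a site follows.

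The expansion of SAE is a separate clerical error. A severe event could not be graded mild, and calling it an effect presumes the causality still to be assessed. No reporting rule is shown to depend on it.

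**What to change.** Reconcile the sentences in Reporting of adverse events:

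- State that the exemption for SAEs plainly due to the underlying disease applies only to onward reporting to the Ethics Committee.
- State that every SAE, whatever its attribution, is documented, sent to the sponsor within the existing 24 h limit, assessed for causality by the sponsor as well as the investigator, and recorded by arm.
- In the list of abbreviations, correct the expansion of SAE so that seriousness and severity are kept apart.

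The cost is a wording change in the protocol and some extra SAE entries by the sites. Design, sample size and efficacy analysis are unaffected.
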